### 1.5 Resonant Convergence: ICR Detuning and Thermodynamic Failure

To unify the impact of low-intensity EMR, developmental anomalies in grey matter, and the mitochondrial-microglial cascade, we propose that ASD should be fundamentally interpreted as a pathology of electrodynamic tuning and thermodynamic coherence, according to the Resonant Convergence model [57].

Maintaining precise neural timing and long-range synchronization — such as the specific phase-locking required by the MNS — relies on highly synchronized transmembrane ion fluxes. According to the Ion Cyclotron Resonance (ICR) model [63,64,65,66], the physiological movement of key ions, particularly Ca^2+^, is only partially concentration-dependent and is instead highly tuned by endogenous electromagnetic fields. This tuning ensures the ultra-fast synaptic responses and network oscillatory entrainment required for instantaneous social referencing.

As formalized in Eqn. 1, these exogenous low-frequency fields act as continuous perturbations on the delicate ICR tuning of transmembrane Ca^2+^ flux, which the Resonant Convergence model links to Ca^2+^/calmodulin- and CaMKII-dependent MNS phase-locking [57]. Within this framework, loss of resonant coherence is further conceptualized through a nonequilibrium thermodynamic lens linking cellular energy dissipation to electromagnetic responsiveness [21,22,23] (full formalism in **Appendix A.1**): the metabolic collapse and ROS accumulation described above are postulated to drive affected neurons into a state of entropic ‘thermodynamic chaos’, chronically distorting the endogenous magnetic microenvironment required for physiological ICR tuning (Fig. 2). This mechanism confronts a well-established theoretical objection — the incompatibility between weak-field Lorentz forces and physiological thermal noise (kT), first formalized by Adair [67,68,69] — which is explicitly acknowledged, not dismissed. ICR and TR are treated throughout this protocol as candidate, Tier-3 frameworks; the full thermal-noise and quantum-coherence-domain debate is presented in **Appendix A.2**. Critically, the protocol’s epidemiological objective is decoupled from resolution of this unresolved transduction debate.

**Fig. 2. F002:**
[figure not shown]
**Resonant convergence multiaxis model**. Resonant Convergence integrative model: four convergent pathogenic axes — genetic, bioenergetic, electrodynamic, and environmental — converging on Ca^2+^-calmodulin-mediated MNS synchronization failure as the common pathophysiological node in ASD. ANS, autonomic nervous system; HRV, heart rate variability; mTOR, mechanistic target of rapamycin.

The MNS requires extremely rapid, coherent phase-locking — particularly in the mu and gamma bands — to guarantee instantaneous imitation and empathy [4,6,53]. We hypothesize that an initial disruption of calcium ICR tuning — induced by exogenous EMFs on developing networks — triggers a catastrophic cascade of mitochondrial dysfunction and oxidative stress [59,61]. This resulting redox imbalance acts on two converging fronts: structurally, it shifts microglia toward pathological synaptic pruning, altering the physical connectome [16]; electrodynamically, it generates an internal thermodynamic noise that irreversibly detunes the physiological Ion Cyclotron Resonance of the neuronal networks [1,11,15,16,18,21,22,63,64,65,66]. This dual structural and electrodynamic disconnection prevents the long-range phase-locking of the MNS, translating clinically into the core social, communicative, and cognitive deficits characteristic of ASD [5,11,18,31,57].

### 1.6 Study Rationale, Primary Hypothesis, and Objectives

Considering the evidence reviewed above, we advance the primary hypothesis that chronic anthropogenic EMR exposure during the first 2 years of life — particularly during sleep phases of heightened synaptic consolidation — constitutes a modulatory etiological cofactor in ASD pathogenesis, acting through ICR detuning of the Ca^2+^/CaM pathway and consequent impairment of MNS synchronization.

To empirically test this hypothesis, this prospective longitudinal pilot study focuses on the critical first 2 years of brain maturation. Rather than establishing direct causality at this stage, the operational objective is to evaluate whether a systematic reduction of EMR exposure during sleep phases can mitigate the incidence or severity of ASD. The study prospectively follows 1000 full-term newborns (gestational age ≥37 weeks) for 24 months. Infants with major congenital neurological abnormalities, severe genetic syndromes, or prolonged neonatal intensive care hospitalization (>14 days) are excluded.

The primary epidemiological objective—assessing whether systematic sleep-phase EMR reduction lowers ASD incidence or severity—is empirically testable independent of the eventual validation of the biophysical mechanisms. ICR and TR are invoked here as heuristic explanatory models for the hypothesis, not as prerequisites for the epidemiological test.

### 2.2 Exposure Control and Environmental Monitoring

The two observational cohorts are managed as follows:

• EMR-Reduced Cohort (n = 500): Subjects are raised under conditions designed to minimize electromagnetic exposure during rest and sleep, targeting the phases of highest synaptic consolidation (Fig. 3). Interventions include the installation of silver-coated, grounded Faraday canopy nets around sleeping areas, the removal of any wireless transmitting devices within the shielded space (e.g., Wi-Fi routers, baby monitors) and the preferential use of wired communication infrastructure in the room.

• Standard Exposure Cohort (n = 500): Subjects reside in typical modern residential environments without specific electromagnetic shielding interventions.

**Fig. 3. F003:**
[figure not shown]
**Critical vulnerability window**. Temporal overlap between MNS maturation, grey matter acceleration, and EMR exposure during the first 24 months, highlighting the proposed sleep-phase shielding window.

To ensure high-fidelity adherence within the EMR-Reduced cohort, the Faraday canopy nets will be equipped with embedded continuity sensors and radio-frequency identification (RFID) tags, providing objective, continuous shield-integrity monitoring. Study staff will provide standardized training to participating families on proper canopy installation and maintenance at enrollment, with structured in-home compliance verification visits conducted quarterly throughout the 24-month follow-up period. This automated technical data stream will be cross-validated on a monthly basis against parent-reported compliance logs and wearable dosimeter data, thereby minimizing reliance on self-reported metrics alone and establishing a multi-layered, objective exposure verification matrix.

### 2.3 Outcome Measures and Covariates

Because neurodevelopment during infancy is more sensitively characterized by continuous developmental measures than by a binary diagnostic outcome, the primary endpoint consists of a predefined composite continuous score integrating joint attention (Early Social Communication Scales; ESCS), early receptive and expressive language development (Communicative Development Inventories [CDI] and/or Mullen Scales of Early Learning [MSEL]), and electroencephalographic (EEG) mu-rhythm spectral power (8–13 Hz) [53]. This composite endpoint will be analyzed longitudinally using linear mixed-effects models, thereby maximizing statistical power while accounting for repeated within-subject measurements over the 24-month follow-up period.

A binary diagnosis of Autism Spectrum Disorder at 24 months, established according to ADOS-2, ADI-R, and Diagnostic and Statistical Manual of Mental Disorders, Fifth Edition (DSM-5) criteria, will constitute a prespecified secondary exploratory endpoint. Because the expected number of ASD cases is relatively small, this outcome will be analyzed using Firth’s penalized logistic regression to minimize small-sample and rare-event bias [70].

To estimate the independent association between EMR exposure and neurodevelopmental outcomes, while minimizing potential confounding arising from parental health-seeking behavior and other selection factors, multivariable regression models will be used. These will adjust for predefined covariates, including a standardized parental socioeconomic status index, objectively recorded child screen-time exposure, and baseline parental health anxiety assessed using the Short Health Anxiety Inventory (SHAI). Additional prespecified clinical and perinatal covariates will be incorporated where appropriate.

All neurodevelopmental assessments, including ADOS-2, ADI-R, and EEG acquisition and analysis, will be performed by trained evaluators blinded to cohort allocation in a standardized clinical environment designed to minimize inadvertent disclosure of exposure status. Video recordings and EEG datasets will be independently coded by assessors blinded to study arm, and inter-rater reliability will be formally evaluated and reported.

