### 1.2 Neural Network Development and the Critical Vulnerability Window

Early childhood — especially the window between 6 and 18 months — is a critical period for the maturation of the MNS and, in general, grey matter [24,25,26,27]. During this developmental phase, infants undergo rapid changes in: imitation ability [25], joint attention [24], eye-gaze synchronization [24], early language acquisition [24], emotional resonance and social referencing [26]. All of these behaviors depend on tightly synchronized interactions between visual perception, motor planning, and limbic regulation — domains strongly overlapping with MNS-related circuits in the inferior frontal gyrus, inferior parietal lobule, and superior temporal sulcus [24,25]. Because these networks rely on precise spike-timing-dependent plasticity and oscillatory synchronization, they are particularly vulnerable to disturbances in neural timing and connectivity during early development [13].

Altered connectivity between MNS regions and other brain areas has been shown to disrupt the integration of social information [2,12]. Very importantly for the sake of our study, Dapretto et al. [6] demonstrated reduced activation in the Inferior Frontal Gyrus (IFG), a key mirror neuron region, during imitation tasks in children with ASD compared to typically developing controls. At the oscillatory level, the most common findings include: reduced delta amplitude [4] and reduced oscillatory coherence in the mu rhythm (8–13 Hz). This last phenomenon is a typical electrophysiological signature associated with mirror neuron activation [4,6]. Moreover, impairment in the formation of predictive coding loops is evident. These phenomena appearing in sensorimotor cortices prevent infants from anticipating other people’s actions and intentions [13]. Lastly, reduced activation of the IFG might produce errors in social reward timing, making eye contact and shared attention less reinforcing [28].

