### 1.4 Biophysical Mechanisms: VGCC Activation, Ca^2+^ Overload, and the Mitochondrial-Microglial Axis

The developing brain exhibits intrinsic oscillatory frequencies (delta, theta, alpha, gamma) [42]. It has been hypothesized that temporally modulated EM signals could entrain or interfere with endogenous neural rhythms through resonance phenomena [43]. While robust macroscopic resonance at environmental RF intensities remains debated *in vivo* due to tissue shielding and thermal regulation [44,45], the biological impact of low-intensity EMR has been empirically documented across multiple domains, including motor tremor [46], reaction time alterations [47], sleep pattern disruptions [48], and indirect EEG modulation [49,50], as well as broader developmental outcomes [51]. Consequently, environmental EMFs represent a critical exogenous trigger for developing neural networks. Because MNS maturation relies strictly on precise spike-timing-dependent plasticity (STDP) [52], alpha/mu synchronization [53], and experience-dependent calibration [54,55], any environmental factor modulating these calcium-dependent learning processes can theoretically interfere with early social-cognitive circuitry [35,56]. In accordance with the Resonant Convergence model, the primary biophysical transducer that explains these diverse EMR-induced alterations is the voltage-gated calcium channel (VGCC) [57]. The modulation of VGCCs by external electromagnetic fields occurs through the alteration of their gating probability, which directly impacts intracellular Ca^2+^ flux [39]. A minor depolarization bias can initially amplify physiological signaling cascades, increasing N-methyl-D-aspartate (NMDA) receptor sensitivity and the activation of cAMP response element-binding protein (CREB) — a crucial transcription factor that regulates the expression of genes involved in synaptogenesis and synaptic plasticity [58]. However, sustained or anomalous activation by low-intensity EM fields leads to deleterious intracellular Ca^2+^ elevation. Crucially, this EMR-induced calcium overload is strictly transduced through the Ca^2+^-calmodulin (CaM) complex [57]. As a primary intracellular sensor, the Ca^2+^/CaM complex activates downstream effectors including calcium/calmodulin-dependent protein kinase II (CaMKII). This kinase is fundamental for synaptic scaling and the long-range phase-locking of the MNS [57]. Under the Resonant Convergence framework, the ICR-detuning of the Ca^2+^/CaM pathway is hypothesized to be the critical biophysical node disrupted by anthropogenic EMR, leading to the theoretically predicted electrodynamic decoupling.

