## 3. Discussion

The present study protocol translates the Resonant Convergence framework [57] into a prospective epidemiological investigation, shifting from genetic determinism to a dynamic Gene-Environment interaction paradigm to test whether EMR acts as a modulatory cofactor in ASD pathogenesis via ICR detuning of the Ca^2+^-CaM pathway. Although this framework offers coherent multi-scale integration, its applicability to infant connectome development remains theoretically grounded; this pilot study is therefore conceived as an initial *in vivo* test of these biophysical models, not as their presupposition. Crucially, its core public health utility rests on the empirical testing of exposure reduction — independent of ICR/TR validation — as a significant neurodevelopmental divergence between cohorts would constitute a medically vital endpoint irrespective of mechanistic confirmation.

The following sections discuss the expected impact of a positive finding and the inherent methodological limitations.

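### The primary composite mixes EEG mu power with joint attention and language, and the Discussion's planned reading of a positive result does not require behaviour to differ

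*Protocol article*

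**What the plan says.** Section 2.3 states that "the primary endpoint consists of a predefined composite continuous score integrating joint attention", measured with the ESCS, together with "early receptive and expressive language development (Communicative Development Inventories [CDI] and/or Mullen Scales of Early Learning [MSEL"]) and "electroencephalographic (EEG) mu-rhythm spectral power (8–13 Hz"). The score is analysed with linear mixed-effects models (Sections 2.3 and 2.5). Binary ASD at 24 months is a separate, secondary exploratory endpoint.

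On the role of the mu rhythm, Section 1.2 reports reduced mu-band coherence in ASD and adds: "This last phenomenon is a typical electrophysiological signature associated with mirror neuron activation". The primary hypothesis in Section 1.6 has exposure "acting through ICR detuning of the Ca^2+^/CaM pathway and consequent impairment of MNS synchronization". Section 1.4 lists "indirect EEG modulation [49,50"] among effects of low-intensity EMR that it regards as documented.

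On what the study is meant to answer, Section 1.6 gives the epidemiological objective as lower ASD incidence or severity, and says that this "is empirically testable independent of the eventual validation of the biophysical mechanisms".

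On how a positive result would be read, the opening of Section 3 says that "a significant neurodevelopmental divergence between cohorts would constitute a medically vital endpoint irrespective of mechanistic confirmation". Section 3.1 then describes a new primary prevention strategy, with shielding recommendations for families.

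**The concern.** Two of the three domains in the score describe what the child does, namely shared attention and language. The third is a brain signal that the plan's own rationale places between exposure and behaviour. A difference in the pooled score can therefore come from behaviour, from the EEG, or from both, and the composite p-value does not say which.

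This matters because the objective is ASD incidence or severity, and mu power is neither. If only the EEG component moved, the score could still be significant. Nothing in Sections 3 or 3.1 would then stop the result from being presented as a medically important developmental divergence and used to support advice to parents, although communication and language were the same in both cohorts. The mixing also works the other way: a real behavioural difference is diluted if mu power does not move.

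**Working it through.** **The plan's own figures.** The article gives no power figure for the composite. Its only power figures (Table 1) are for binary ASD by Fisher's exact test with 500 per arm. Exact enumeration gives 10.26%, 27.04%, 57.34% and 75.11%, against the stated 10.3%, 27%, 57.2% and 75%. Table 1 is therefore sound, but it does not bear on this point.

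**Inputs for the illustration.**
- From the article: 500 per cohort (Section 2.1) and attrition of 20–22% (Section 2.5). At 22%, 500 × 0.78 = 390 per cohort.
- Assumed, because the article does not give them: three equally weighted z-scores (joint attention, language, EEG), common pairwise correlation r of 0.1–0.5, a single time point, no covariates or weighting, and no behavioural effect. Two-sided α = 0.05 is stated only for the binary outcome and is carried over here.

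**Formulas.** An EEG-only shift of d SD moves the mean of three z-scores by d/3. The SD of that mean is √((1 + 2r)/3). The standardised composite difference is D = (d/3) / √((1 + 2r)/3). Power ≈ Φ(D·√(n/2) − 1.96), with √(390/2) = 13.96.

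Worked case, d = 0.5 and r = 0.3: the SD is √(1.6/3) = 0.730, so D = 0.1667/0.730 = 0.228. Then 0.228 × 13.96 = 3.19, and Φ(3.19 − 1.96) = Φ(1.23) = 0.89.

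| EEG-only shift (SD) | r = 0.1: D, power | r = 0.3: D, power | r = 0.5: D, power |
|---|---|---|---|
| 0.2 | 0.105, 31% | 0.091, 25% | 0.082, 21% |
| 0.3 | 0.158, 60% | 0.137, 48% | 0.122, 40% |
| 0.5 | 0.264, 96% | 0.228, 89% | 0.204, 81% |

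**Sensitivity.** The EEG-only shift that gives the composite 80% power, for r from 0 to 0.6:
- Three components: 0.35–0.52 SD at 390 per cohort, or 0.31–0.46 SD at 500.
- Four components (receptive and expressive language counted separately): 0.40–0.67 SD at 390, or 0.35–0.59 SD at 500.

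**The reverse case.** Suppose joint attention and language each differ by 0.2 SD and mu power does not differ, with 390 per cohort.
- Behaviour-only score: D = 0.2/√((1 + r)/2) = 0.270 (r = 0.1) to 0.231 (r = 0.5), so power is about 96% to 90%.
- Three-part composite: D = (0.4/3)/√((1 + 2r)/3) = 0.211 to 0.163, so power is about 84% to 63%.

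**The case against.** A reader might infer that the plan contradicts itself by claiming independence from mechanism and then putting a mechanism marker in the primary score. The text does not support that. Sections 1.5, 1.6 and 3 separate the epidemiological question from the ICR/TR transduction debate, not from the mirror neuron system. Mu power tests neither ICR nor TR, and Section 1.2 presents altered mu rhythm as a finding in ASD itself. On the plan's terms it is a relevant neurodevelopmental measure.

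A reader might also infer that the Discussion declares any significant composite to be a benefit. It does not use that word, and the sentence names neither the composite nor the primary endpoint. Section 3.2 says that the pilot is not meant to support definitive clinical conclusions, and ASD diagnosis is assessed separately.

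Other points also stand. The EEG effect cited in Section 1.4 is unspecific: it names neither mu power nor infants. Shielding applies during rest and sleep, whereas EEG is recorded in a clinic by blinded staff, so an EEG difference would have to outlast the home exposure. The weights may be set in a full protocol or SAP. A single-time comparison is neither the planned mixed model nor the weighted marginal structural model of Section 3.2. With a small EEG shift the composite is usually not significant. Finally, any composite can be driven or diluted by one component, and combining behaviour with neurophysiology is a legitimate choice.

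None of this supplies the missing condition. Blinding protects the measurement, not the meaning of the score. The caution in Section 3.2 sits beside the prevention claims of Section 3.1 without limiting them to a result in which behaviour differs.

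**Conclusion.** The point holds as one of interpretation. The primary score can be significant through mu power alone, and the article does not require a behavioural difference before a divergence is called medically vital or used to support prevention advice. That falls short of the stated objective of ASD incidence or severity.

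The size depends on assumptions that the article does not give. Under those set out above, the chance of a significant composite with no behavioural effect runs from about 21–31% for a 0.2 SD EEG shift to about 81–96% for 0.5 SD. Other weights would change these figures. The problem of reading remains for any material EEG weight.

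It would go too far to conclude that mu power must leave the primary score. Removing it trades away any power that it adds, and reasonable statisticians would differ.

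**What to change.** Keep the composite if the sponsor prefers it. Prespecify two supporting analyses with the same model as the composite: the ESCS-plus-language sub-score, and EEG mu power on its own.

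Revise the opening of Section 3 and Section 3.1. A composite difference should be called a medically vital neurodevelopmental divergence, or be used to support prevention advice, only if the behavioural sub-score differs in the same beneficial direction. Otherwise it should be reported as an electrophysiological difference.

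The cost is one extra model for each of the two parts and some rewording, with no new data. The claim becomes narrower if only the EEG moves. Making the primary score behavioural and mu power a named secondary endpoint is an option for the sponsor, not a required correction.

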### 2.4 Genetic Susceptibility and Genomic Analysis

Baseline familial risk is documented through family history to distinguish genetically predisposed populations. Furthermore, the study incorporates an optional genomic screening component to evaluate Gene–Environment interactions. This screening targets candidate genes involved in biological pathways theoretically vulnerable to specific ELF-EMF modulation, including synaptic structure, neuroinflammation, circadian regulation, mitochondrial metabolism, and neurotransmitter signaling.

This gene-environment interaction framework is directly supported by recent experimental data demonstrating that RF exposure upregulates ASD-associated genes—including TBR1, ARX, FOXG1, and SCN2A—in human fetal cortical organoids via BET-mediated epigenetic mechanisms [35]. The broader candidate frequency-gene associations, with methodological details, full tables, and associated references, are moved to **Appendix A.3**. Within the Resonant Convergence framework, these associations are classified strictly as Tier-3 hypotheses—defined as biologically plausible and supported by preliminary observational data, yet lacking established, direct mechanistic confirmation in the human context [57]. Accordingly, the genomic screening component of this protocol is primarily exploratory and hypothesis-generating; it is not designed for causal inference, and the specific relationships hypothesized in **Appendix A.3** should not be construed as validated clinical or dosimetric guidance. As further detailed there, with the sole exception of the ADORA2A/3–75 Hz pairing—the only target supported by direct *in vitro* EMF evidence [71]—all other candidate frequencies represent theoretical extrapolations derived from the general ICR framework rather than gene-specific empirical findings.

